## Abstract

**Introduction:**

Non-pharmacological therapies in traditional Chinese medicine (TCM) play an important role in the management of nonspecific chronic neck pain (NCNP). Tuina therapy and Baduanjin exercise, representing passive and active modalities, respectively, have shown benefits in reducing pain, improving cervical mobility, and enhancing quality of life. However, the therapeutic efficacy of Tuina combined with Baduanjin (TCB) approach for NCNP remains insufficiently elucidated. This study aims to determine whether TCB provides superior effects in pain relief and functional outcomes compared with Baduanjin exercise alone.

**Methods and analysis:**

A total of 110 NCNP patients aged 18 to 50 years will be recruited. Participants will be randomly assigned in a 1:1 ratio to either the TCB group or Baduanjin group. Each group will undergo a total of 16 sessions of therapy over 8 weeks, with two sessions per week. Outcomes will be assessed at week 8, 20, and 32 post-randomization. The primary outcome is the pain intensity at week 8, assessed by the visual analogue scale scores (VAS). Secondary outcomes include functional disability (evaluated with the Neck Disability Index), quality of life (assessed using the 12-item Short Form Survey questionnaire), emotional distress (measured by the Hospital Anxiety and Depression Scale), sleep quality (evaluated with the Pittsburgh Sleep Quality Index), work efficiency (assessed using the Work Productivity and Activity Impairment Questionnaire-Specific Health Problem), and safety. The statistical analyses will follow the two-way repeated measures analysis of variance to compare clinical data between groups across different time points.

**Ethics and dissemination:**

The study protocol has received approval from the Ethics Committee of Yueyang Hospital of Integrated Traditional Chinese and Western Medicine, Shanghai University of Traditional Chinese Medicine (2023-143). All study participants will be required to provide written informed consent. The findings of the study will be submitted to a peer-reviewed journal for publication and presented at scientific conferences. Additionally, the participants will receive copies of the results upon requests.

**Clinical Trial Registration**: https://www.chictr.org.cn/, identifier (ChiCTR2300073680).

## Introduction

1

Nonspecific chronic neck pain (NCNP) is a prevalent condition defined as pain localized to the cervical spine and/or shoulders persisting for more than three months in the absence of identifiable structural abnormalities and is frequently accompanied by motor dysfunction (1). Largely driven by prolonged forward head posture, the global prevalence of NCNP has been rising in recent years, reaching up to 25% in economically developed regions (2, 3). Beyond its high prevalence, NCNP is frequently accompanied by anxiety, depression, and insomnia, leading to diminished quality of life, reduced work productivity, and substantial economic burden (4, 5). In addition to first-line pharmacological agents, such as non-steroidal anti-inflammatory drugs and muscle relaxants (6, 7), various non-pharmacological therapies—including exercise, transcutaneous electrical nerve stimulation, kinesiotherapy, Tuina (traditional Chinese manual therapy), and acupuncture—have been widely applied and demonstrated clinical benefits (8–10).

Tuina involves both soft tissue and spinal manipulations (11). Soft tissue techniques include pressing, pushing, kneading, stroking, friction, and drumming, whereas spinal manipulation is typically characterized by high-velocity, low-amplitude thrusts (12). A systematic review and meta-analysis found that, Tuina significantly reduced neck pain [pooled standard mean difference (SMD) 1.79, 95% confidence intervals (CI), 1.01 to 2.57, *p* < 0.0001] when compared with inactive controls such as waiting list or standard care (13). Baduanjin is a traditional Chinese mind-body exercise that promotes physical and mental health and alleviates illness (14). It consists of a series of structured movements designed to regulate breathing, reduce muscle tension, and enhance joint mobility. Several studies have demonstrated that Baduanjin can alleviate neck pain, improve cervical spine mobility (15–17), and reduce symptoms of anxiety and depression (18). However, controversy regarding efficacy remains due to small sample sizes, methodological limitations, inadequate quality control, low treatment precision, and short follow-up durations (19). Research suggests that combination therapies are often recommended in clinical practice to overcome the limitations and short-term effects of monotherapy (20). Although evidence supports the efficacy of Tuina and physical activity in improving symptoms and psychological outcomes in NCNP, high-quality randomized controlled trials (RCTs) evaluating the combined effects of Tuina and Baduanjin, particularly with long-term follow-up, remain scarce (21, 22).

This RCT aimed to evaluate the efficacy of TCB in reducing pain, disability, and psychological distress in patients with NCNP, with findings expected to clarify whether TCB is superior to Baduanin alone.

## Methods

2

### Study design

2.1

This study is a randomized, assessor-blinded, single-center, two-arm, parallel-group superiority trial. The protocol was approved by the Ethics Committee of Yueyang Hospital of Integrated Traditional Chinese and Western Medicine, Shanghai University of Traditional Chinese Medicine (project number: 2023-143), and registered at the Chinese Clinical Trial Registry (ChiCTR2300073680). This study will follow the strict criteria outlined in the Consolidated Standards of Reporting Trials (CONSORT) and the Standard Protocol Items: Recommendations for Interventional Trials (SPIRIT) guidelines.

A total of 110 participants will be recruited from the Tuina Department of Shanghai Yueyang Hospital and randomly assigned (1:1) to either the Baduanjin group or the TCB group. The trial includes an 8-week intervention period and a 24-week follow-up. Baseline characteristics will be collected prior to randomization, and outcomes (pain, functional impairment, quality of life, adverse events) will be assessed at weeks 8, 20, and 32. The study procedures are illustrated in a flowchart (Figure 1), with the intervention and outcome schedule detailed in Table 1.

**Figure 1 F1:**
[figure not shown]
Flowchart of the study. TCB, Tuina combined with Baduanjin.

**Table 1 T1:** Schedule of enrolment, intervention and outcome measures.

	Enrolment and allocation				
	Screening	Allocation	Treatment period	Follow-up period	
Timepoint	Week-1	Week 0	Week 8	Week 20	Week 32
Enrolment					
Eligibility	x				
Demography	x				
Informed consent	x				
Medical history	x				
Physical examination	x				
Allocation		x			
Intervention					
Baduanjin			x		
TCB			x		
Outcomes					
VAS	x		x	x	x
NDI	x		x	x	x
SF-12	x		x	x	x
HADS	x		x	x	x
PSQI	x		x	x	x
WPAI-SHP	x		x	x	x
Adverse events			x		

TCB, Tuina combined with Baduanjin; VAS, Visual Analog Scale; NDI, Neck Disability Index; SF-12, 12-item Short Form Survey; HADS, Hospital Anxiety and Depression Scale; PSQI, Pittsburgh Sleep Quality Index; WPAI-SHP, Work Productivity and Activity Impaimrment Questionnaire: Specific Health Problem.

### Participants recruitment

2.2

Participants will be recruited through posters in the Tuina Department and advertisements on WeChat, the largest social media platform in China. The poster includes the project title, participant inclusion and exclusion criteria, and contact information, including the recruiter's phone number, WeChat QR code, and address.

The clinical research coordinator (CRC) is responsible for explaining the study protocol and eligibility criteria and conducting a preliminary eligibility assessment for interested individuals. Potentially eligible participants will receive informed consent documents via email, WeChat, or in person, with sufficient time provided for review before making a decision. Eligible participants who confirm interest will attend a baseline visit, where an investigator will review the study protocol, reconfirm eligibility, and obtain written informed consent. To mitigate potential recruitment barriers related to access to Tuina therapy, participants randomized to the Baduanjin group will be assured free Tuina therapy upon completion of the trial. Baseline assessments will include all primary and secondary outcomes along with demographic data, after which participants will be randomized.

### Inclusion criteria

2.3

Eligible participants who meet the following criteria will be enrolled:
Age between 18 and 50 years old, both male and female.The primary complaint of pain in the neck region, which starts at the superior nuchal line and continues down to the level of the scapular spine.NCNP lasting for at least 3 months, with no specific signs of neurological damage or whiplash injury, as defined by the British Medical Journal guidelines.The average score on the visual analog scale (VAS, scale range, 0–10) over the past week between 3 and 7.The scores of the neck disability index (NDI, scale range, 0–50) of ≥10.Voluntarily participate in the trial and sign the informed consent.

### Exclusion criteria

2.4

Participants who fulfill the subsequent criteria will be excluded:
History of cervical intervertebral disc herniation with associated peripheral nerve symptoms, neck trauma, surgical neck fracture, spinal disease, infectious inflammatory autoimmune diseases, congenital vertebral anomalies; or compression fractures of any location sites.With abnormal neck appearance, including scars, hyperpigmentation, and papules.With organic illnesses, such as malignancy, cardiovascular, cerebrovascular, liver, kidney, or genetic disorders.With mental illnesses, such as anxiety, depression, persecution delusion, and schizophrenia.Current or past history (within 12 months of screening) of infectious diseases, alcohol, drug, or medication abuse.Participation in other clinical trials within 3 months prior to enrolment.Regularly participated in neck pain exercise training over the past 3 months, defined according to the WHO guidelines as more than 150 min of exercise per week (23).Utilization of any other therapy within 1 month (drug or non-drug).Women who are pregnant or lactating or planning a pregnancy.Surgical strategy for the subsequent 8 months.Not willing to accept or have adverse reactions to Tuina therapy.The exclusion criteria will apply to individuals who meet one or more of the aforementioned requirements.

### Withdrawal, dropout and removal criteria

2.5

Participants may withdraw from the trial at any time or be discontinued under the following circumstances, as determined by the clinical Data Monitoring Committee (DMC):
Clinically significant exacerbation of NCNP symptoms that severely impairs daily functioning or safety.Unanticipated serious adverse events or complications occur during the trial period, including trauma, allergic reactions, or worsening pain.Occurrence of other serious illness precluding continued participation, such as stroke, hospitalization, surgical interventions, or emergency care.Unblinding for emergencies.Withdrawal deemed necessary at the discretion of the researchers.Participants request to withdraw from the study due to a loss of interest, scheduling conflicts or other personal reasons.We will strive to contact participants who withdraw for any reason to acquire follow-up data and ensure their safety post-trial.

### Randomisation, allocation concealment and blinding

2.6

An independent statistician generated the computer-based randomization sequence and prepared sequentially numbered opaque envelopes (SOEs) containing group assignments to ensure allocation concealment. An independent CRC stored and distributed the SOEs, while investigators remained blinded to group allocation. Following informed consent and baseline assessment, a designated researcher will assign each participant a unique study ID and open the corresponding envelope to reveal the allocation (“Baduanjin” or “TCB”). Given the nature of the interventions, intervention implementation personnel and participants cannot be blinded to group allocation. Evaluators, data entry personnel, and statisticians will remain blinded throughout the study to ensure objectivity.

### Sample size calculation

2.7

The sample size was determined for the primary outcome, mean pain intensity over the past week measured by the 0–10 VAS at 8 weeks post-randomization. We made an assumption of the anticipated between-group mean difference and standard deviation (SD) for the primary outcome (VAS) based on both literature and internal review of electronic patient records. An effect size of −1.2 points (95% CI, −1.6 to −0.8) was reported for tuina therapy combined with Yijinjing exercise (24) (a different exercise than Baduanjin, but also based on traditional Chinese exercise) compared with tuina therapy alone. Previous literature confirmed that for the measurement of bone and joint pain, 1.5 points can represent clinically important difference (MCID) (25). Due to the lack of direct previous research results on Tuina with or without Baduanjin, we set the smallest threshold difference than the results from literature or real-world data suggest. Therefore, a between-group difference of −1.5 in mean change at Week 8 and standard deviation1.1 to calculate the sample size. Calculations were performed using PASS 15 software with reference to Sample Size Calculations in Clinical Research (26). Assuming two groups, a two-sided significance level of 0.05, 80% power, and a 80% follow-up rate, 55 participants per group were required, yielding a total sample size of 110.

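### The planned 55 per group does not follow from the stated sample size inputs, which need only 12 to 13 per group

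*Protocol article*

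**What the plan says.** Section 2.1 (Study design) describes a "randomized, assessor-blinded, single-center, two-arm, parallel-group superiority trial" with participants "randomly assigned (1:1) to either the Baduanjin group or the TCB group". Section 2.7 (Sample size calculation) sizes it on "mean pain intensity over the past week measured by the 0–10 VAS at 8 weeks post-randomization" and gives every input the calculation needs:

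- difference and SD: "a between-group difference of −1.5 in mean change at Week 8 and standard deviation1.1 to calculate the sample size"
- error rates, follow-up and result: "Assuming two groups, a two-sided significance level of 0.05, 80% power, and a 80% follow-up rate, 55 participants per group were required", for a total of 110.

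Section 2.7 states no superiority margin, design effect or multiplicity adjustment.

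To justify the difference, the section quotes one published estimate, −1.2 points (95% CI −1.6 to −0.8), for Tuina plus a different traditional exercise against Tuina alone. It also cites a 1.5-point MCID. It then says of its own choice: "we set the smallest threshold difference than the results from literature or real-world data suggest".

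**The concern.** A difference of 1.5 with an SD of 1.1 is a standardised difference of 1.5/1.1 = 1.36, which is very large. A plain two-group comparison detects an effect of that size with few participants, so 55 per group at only 80% power looks far too many.

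At stake is what the trial was designed to detect. If the SD is 1.1, the study has near-certain power for 1.5 points and can reach significance on differences well below its own MCID. If 55 came from a larger SD, the published SD is wrong and the trial has only about the power claimed. The results are to be read against the 1.5-point MCID (section 2.11 and the Discussion), so readers need to know which of these holds.

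The rationale adds to the doubt. It appears to present 1.5 as a cautious choice relative to the evidence, yet 1.5 is larger than the only estimate quoted, 1.2.

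**Working it through.** **Inputs (all from section 2.7, with 1:1 allocation from section 2.1).** Difference δ = 1.5; SD σ = 1.1; two-sided α = 0.05 (z = 1.96); power 80% (z = 0.8416); follow-up 80%.

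**Step 1: attempt to reproduce the plan's figure.** Evaluable participants per group:

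n = 2(z₁₋α/₂ + z₁₋β)² σ² / δ² = 2 × (1.96 + 0.8416)² × 1.1² / 1.5² = 8.44, so 9.

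The t-test version (noncentral t) gives 9.5, so 10.

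Allowing for follow-up: 9/0.8 = 11.25, so 12; 10/0.8 = 12.5, so 13. The total is 24 to 26. The plan's 55 per group is 4.2 to 4.6 times as many (55/13 and 55/12) and is not reproduced.

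**Step 2: other readings of the inputs.** Per group, after follow-up, with everything else as stated:

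| Change | Per group |
|---|---|
| One-sided α | 9 |
| Power 90% | 15–17 |
| Power 99% | 25–27 |
| SD × √2 (uncorrelated change score) | 23 |
| Rank test (efficiency 0.864) | 15 |
| Difference 1.2 (quoted estimate) | 18–19 |
| Difference 0.8 (weakest limit of its CI) | 38–39 |

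None is close to 55.

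**Step 3: locate the mismatch.** 55 × 0.80 = 44 evaluable per group, a whole number, so the follow-up adjustment is consistent. With 44 per group, the standardised difference detectable with 80% power is 2.8016 × √(2/44) = 0.597 (normal) or 0.604 (t), against 1.36 from the stated pair. Back-solving by the normal approximation, one change at a time:

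- δ = 1.5, σ = 2.5: n = 2 × 2.8016² × 2.5²/1.5² = 43.6, so 44, and 44/0.8 = 55.
- σ = 1.1, δ = 0.66: n = 2 × 2.8016² × 1.1²/0.66² = 43.6, so 44, and 44/0.8 = 55.

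With a t-test, both need 45 evaluable, and 45/0.8 = 56.25, so 57.

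**Step 4: what 44 evaluable per group delivers (t-test).**

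| True difference | Power if SD = 1.1 | Power if SD = 2.5 |
|---|---|---|
| 1.5 | above 99.9% | 79.5% |
| 1.2 | 99.9% | 60% |
| 0.8 | 92% | 32% |

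The smallest observed difference that reaches significance is t(0.975, 86) × SD × √(2/44), with t = 1.988: 0.47 points at SD 1.1, and 1.06 points at SD 2.5.

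**The case against.** The arithmetic itself is hard to dispute. The serious objections concern what follows from it.

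- **The trial is not shown to be underpowered.** This stands. For a true difference of 1.5, power is about 80% or more under either back-solution.
- **The faulty input cannot be identified.** This also stands. SD 2.5 and difference 0.66 fit equally well, and both fit exactly only under the normal approximation. An unstated superiority margin of about 0.84 would do the same (1.5 − 0.84 = 0.66). A wrong power figure alone is unlikely to be the source, since even 99% power needs only 25 to 27 per group. Still, 80% is not the power that the stated difference, SD and sample size imply together.
- **The MCID risk is partly covered.** The Discussion says clinical importance will be judged against MCID thresholds, and section 2.11 adds the proportion reaching 1.5 points. Any superiority test against zero can be significant below its design difference. The point about small significant differences is therefore secondary, and it depends on SD 1.1 being true.
- **The rationale sentence is garbled, and the evidence gap is disclosed.** The threshold may refer to the MCID or to internal records that are not shown, and 1.5 lies inside the quoted interval. The section names the comparator of the cited study and admits that direct evidence is lacking. It does not say that the added component is reversed: the cited study adds exercise to Tuina, whereas this trial adds Tuina to exercise. A clarification is fair, but the finding does not rest on this.

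None of this closes a fourfold gap. Nor is it a detail left to a fuller document: the article gives a complete set of inputs and a result that disagree.

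**Conclusion.** The concern holds: the sample size statement is wrong as written. The stated inputs require 12 to 13 per group (24 to 26 in total), against 55 (110). With the stated difference and SD, 110 participants give power above 99.9%, not 80%. The likeliest fault is the SD or the difference as printed, or an input left out; the document does not settle which. The rationale also needs correcting, because 1.5 exceeds the only quoted literature estimate.

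This rests on a standard 1:1 comparison of two means at the stated error rates, with 80% follow-up applied by division. The conclusion does not depend on using the normal or t calculation, nor on the other variants tried.

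**What to change.** Keep the total at 110 and correct section 2.7:

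1. Report the difference, SD, test and any margin actually entered in the software, with the source of the SD. These should come from the calculation record, not be chosen afterwards to fit 55. If the SD used was near 2.5, say so.
2. If SD 1.1 and difference 1.5 are confirmed, withdraw the claim that 55 per group were required for 80% power. State instead that 44 evaluable per group give over 99.9% power for 1.5 points and 80% power for about 0.66 points. In that case, add that a significant difference below 1.5 points will not be described as clinically important.
3. Delete or rewrite the sentence on the smallest threshold, since 1.5 exceeds the quoted 1.2.
4. State that the cited estimate is for adding exercise to Tuina, which is not this trial's contrast.

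The cost is the rewording of one section. Enrolment does not change.

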### Intervention

2.8

Interventions will be conducted in dedicated treatment rooms at Yueyang Hospital by therapists who have undergone standardized training. Participants will receive 16 sessions over 8 weeks with 2 sessions per week and 30-minute per session. The intervention period will last 8 weeks. No further study treatment will be provided thereafter. Outcome assessments at weeks 20 and 32 reflect 12 and 24 weeks post-intervention follow-up. Before the intervention, all participants will receive standardized health education on cervical spine posture, including avoiding vigorous acceleration-deceleration activities, using pillows that support physiological curvature, and minimizing prolonged forward head posture, flexion, or tilting. During the intervention, session attendance will be documented in standardized logs, though no additional experimental data will be collected. Participants who miss sessions will be contacted to determine reasons and encourage adherence. While the use of additional therapies is discouraged but not prohibited, any concomitant treatments will be systematically recorded.

#### TCB group

2.8.2

The Tuina intervention will be performed by three licensed Tuina physicians from the Tuina department of Yueyang hospital. To ensure treatment standardization, a 12 h technical training program will be conducted over two weeks (three sessions per week), comprising lectures, video demonstrations, and practical exercises. Following training, physicians will undergo an assessment, with only those who pass deemed eligible to deliver the intervention. Training and evaluation will be supervised by [name], editor-in-chief of the Chinese Tuina National Planning Textbook and an expert with extensive clinical and teaching experience.

The Tuina intervention will last 20 min and comprise three sequential steps: local manipulation, acupressure manipulation and spinal manipulation. Specifically, rolling, pressing-kneading, plucking and grasping manipulation will be applied for 11 min to relax the muscles of the suboccipital, cervical, shoulder, and upper back regions. Subsequently, acupressure manipulation will be administered to the acupoints—including Fengchi (GB20), Fengfu (DU16), Dazhui (DU14), Jianjing (GB21), Tianzong (SI11) and Jiaji (EX-B2)—for about 1 min per acupoint. Acupoint localization will follow the WHO Standard Acupuncture Point Locations in the Western Pacific Region (ISBN: 9787117123327). Illustrations of the acupoints are provided in the Supplementary Materials, and further details of the intervention are available in online Supplementary File 2.

